### 2.7. Data collection and analysis

The REDCap platform will be used for all data collection and storage. Descriptive analyses will be conducted for the demographics data and group differences at baseline will be analyzed using a Chi-square. 1) A mixed methods repeated measures ANOVA [(within-subject (time) × between-subject (group)] factors will be conducted to evaluate changes in stress (PSS), anxiety (GAD-7), and depression (PHQ-9) scores from baseline to 4-weeks (*primary study endpoint*) in the intervention group vs. waitlist control.

Additional analysis of covariance (ANCOVAs) will control for variables that differ between groups at baseline. All ANOVAs will be tested at two-tailed alpha = 0.05. An additional sensitivity analysis two-way ANOVA will be performed to compare participants who (1) engaged in daily home practice (average of ≥ 10 min, ≥ 4 days/week). Missing data will be handled using the last observation carried forward (LOCF). Analyses will be performed using R statistical software. Additional subgroup analyses will also compare the primary outcome (PSS) between important subgroups [e.g., (remote vs. in-person) and baseline stress (higher vs. lower)].

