**Methods:**

We will recruit 30 participants aged ≥ 60 years, whose perceived stress score (PSS) is > 14 (moderate stress), and randomize them 1:1 to the intervention or control waitlist group. The intervention will involve exposure to eight 15-min VR-guided meditation sessions distributed twice weekly for 4-weeks. Two modalities will be offered: in-home and at the hospital.

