### 2.4. Participants

Potential participants will be contacted and screened for eligibility. The eligibility criteria for participation in the study are outlined in Table 1. A total of 30 older adults (aged ≥ 60) will be recruited from the community, community organizations, and affiliated hospitals/clinics. Written or recorded verbal informed consent will be obtained from all eligible participants prior to study initiation. Participants will be randomized 1:1 into the treatment group (receiving the VR meditation immediately) or the waitlist control group (receiving the VR meditation after 4 weeks—*primary study endpoint*). Baseline assessments will be completed using REDCap and an introductory digital literacy session will be provided to help the participant familiarize themselves with the technology, and assist with the setup of headsets.

**Table 1 tab1:** Eligibility criteria.

Inclusion criteria	Exclusion criteria
(1) Aged ≥ 60 years old	(1) Diagnosis of epilepsy, schizophrenia, brain tumor
(2) Ability to speak in English or French	(2) Recurrent migraines, seizures or traumatic brain injury (TBI) in the last year
(3) Ability to provide consent (4) Residing in the Greater Montreal area	(3) Diagnosis of a substance use disorder in the last year
(5) Having a Perceived Stress Score (PSS) greater than 14	(4) Psychiatric hospitalizations in the last year
	(5) Acute psychotic symptoms or suicidal ideation/intent
	(6) Glaucoma or recovery phase of any eye surgery
	(7) Post-traumatic stress disorder
	(8) Changes to psychoactive medications in the 4 weeks prior to the study
	(9) Severe hearing impairment
	(10) Consumption of alcohol, caffeine, or cannabis within the last 24 h or nicotine within the last 15 min before a session

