### 2.6. Study outcomes

All quantitative outcomes (primary, secondary, exploratory) will be assessed at baseline and 4 weeks *(primary study endpoint)*, in-person or remotely by phone. All assessments will be administered by an assessor who is blinded to group allocation.

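### With only two assessments, the planned time × group ANOVA is a change-score t-test; pre-specifying ANCOVA on baseline PSS would give a modest, nearly free gain in precision

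*Protocol article*

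**What the plan says.** Section 2.7 names the main comparison: "A mixed methods repeated measures ANOVA [(within-subject (time) × between-subject (group)] factors will be conducted to evaluate changes in stress (PSS", together with GAD-7 and PHQ-9 "scores from baseline to 4-weeks", intervention against waitlist. The level is set there too: "All ANOVAs will be tested at two-tailed alpha = 0.05".

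Section 2.6 limits the data to two occasions: "All quantitative outcomes (primary, secondary, exploratory) will be assessed at baseline and 4 weeks". Section 2.6.1 makes PSS the primary outcome. Section 2.4 gives the size and allocation: "A total of 30 older adults (aged ≥ 60) will be recruited from the community" and "Participants will be randomized 1:1 into the treatment group", so about 15 per arm.

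Baseline adjustment has a secondary and conditional role in section 2.7: "Additional analysis of covariance (ANCOVAs) will control for variables that differ between groups at baseline". Nothing fixes baseline PSS as a covariate in the primary analysis.

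Entry depends on the outcome scale itself. The abstract describes participants "whose perceived stress score (PSS) is > 14 (moderate stress", and Table 1 repeats the threshold.

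**The concern.** With two groups and two occasions, the repeated-measures machinery adds nothing to a comparison of mean change. Analysing change amounts to subtracting the whole baseline score, a slope of 1. When the slope of the 4-week score on baseline is below 1, that subtracts too much. Part of the baseline noise stays in the estimate, along with part of any chance baseline difference between arms. Estimating the slope, as ANCOVA does, removes this.

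The additional ANCOVAs do not meet the point. The gain comes from the correlation between baseline and follow-up and is present even when the arms are balanced. A rule triggered by observed differences leaves the adjusted model unsettled until the data are seen, and it leaves the primary test unadjusted in any case.

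At stake is the width of the interval around the PSS effect in a 30-person trial whose results are meant to inform larger studies.

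**Working it through.** **Inputs from the protocol article.** N = 30, allocated 1:1 (15 per arm); assessments at baseline and 4 weeks; two-sided alpha 0.05; entry at PSS > 14. The article states no power, SD, effect size or correlation, so there is no planned figure to reproduce.

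**Assumptions, not in the article.** Before selection, PSS is normal with mean 20 and SD 7 on both occasions. The effect is 5 points, follow-up is complete, and rho (the correlation before selection) runs from 0.3 to 0.9.

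**Step 1: identity.** In one simulated data set with 15 per arm, the split-plot interaction gave F = 0.70529 and the squared t on change scores gave 0.70529. The two tests are the same.

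**Step 2: baseline spread after selection.** a = (14 − 20)/7 = −0.857. The hazard term is λ = φ(a)/[1 − Φ(a)] = 0.3435. Then V0 = 49 × (1 + aλ − λ²) = 28.79, an SD of 5.4 among entrants. Selecting on baseline leaves the slope of follow-up on baseline unchanged, so it stays at rho.

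**Step 3: variance per participant.**
- Change score: (1 − rho)² × V0 + 49(1 − rho²)
- ANCOVA: 49(1 − rho²) × [1 + 1/(N − 4)], where 1 + 1/26 = 1.0385

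The variance of the treatment estimate is either of these times 2/15. Power is from the noncentral t with noncentrality 5/SE, on 28 df (change) or 27 df (ANCOVA).

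| rho | Change variance | ANCOVA variance | Ratio | SE, change / ANCOVA | Power, change / ANCOVA |
|---|---|---|---|---|---|
| 0.3 | 14.11 + 44.59 = 58.70 | 44.59 × 1.0385 = 46.31 | 0.79 | 2.80 / 2.48 | 41% / 49% |
| 0.5 | 7.20 + 36.75 = 43.95 | 36.75 × 1.0385 = 38.16 | 0.87 | 2.42 / 2.26 | 51% / 57% |
| 0.7 | 2.59 + 24.99 = 27.58 | 24.99 × 1.0385 = 25.95 | 0.94 | 1.92 / 1.86 | 71% / 74% |
| 0.9 | 0.29 + 9.31 = 9.60 | 9.31 × 1.0385 = 9.67 | 1.01 | 1.13 / 1.14 | 99% / 99% |

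**Step 4: check by simulation.** Simulating the same truncated setting gave ratios of 0.80, 0.87 and 0.94, and power of 40% against 49%, 50% against 56% and 71% against 74%, at rho 0.3, 0.5 and 0.7. The formulas agree to within about one percentage point. In a separate truncated simulation (mean 22, SD 8), type I error was about 4.4% to 5.5% for both methods.

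**Step 5: cost and break-even.** The critical t rises from 2.048 to 2.052. The variances are equal when (1 − rho) × 28.79 = (49/26)(1 + rho), which gives rho = (28.79 − 1.88)/(28.79 + 1.88) = 0.88. Above that ANCOVA loses, but never by more than the 1.0385 factor.

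**Step 6: chance imbalance.** The SE of the baseline difference between arms is 5.37 × √(2/15) = 1.96 points. A difference of that size leaves (1 − rho) × 1.96 in the change-score estimate, or 0.98 points at rho 0.5.

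**The case against.** The strongest reply is that nothing here is wrong. The change-score test is unbiased under randomisation and holds its level, and the article makes no power claim that a less efficient test would undermine. This is a pilot with feasibility and acceptability among its aims, and every magnitude above rests on values the article does not give. All of that stands. It makes the point an improvement, not a correction. It does not make the choice neutral, because the article tests PSS at the 5% level and offers the results as a basis for later trials.

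Several stronger readings are tempting but unsupported:

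- **That selecting on PSS pushes the slope below 1.** It does not. The slope is below 1 because baseline and follow-up are imperfectly correlated. The threshold narrows the baseline range and so reduces ANCOVA's advantage.
- **That the textbook ratio (1 + rho)/2 applies**, making ANCOVA at rho 0.5 worth 40 participants instead of 30 (30/0.75). That ignores both the truncation and the small sample. With them the equivalent is about 35 (30/0.868).
- **That the change is free.** It costs one degree of freedom and about 4% in variance.
- **That the plan treats the time or group main effects as evidence of benefit.** Section 2.7 evaluates change in one arm against the other, which is the interaction, and nowhere offers the main effects as evidence.
- **That the plan ignores baseline imbalance.** The additional ANCOVAs could include baseline PSS if it were judged to differ. That is partial, data-dependent cover and does not recover precision in the primary test.

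**Conclusion.** The point holds as a cheap improvement in efficiency and pre-specification; the planned analysis is not invalid. The equivalence to a change-score t-test is exact and needs no assumption. The size of the gain does. With an assumed mean of 20, SD of 7, a 5-point effect and baseline truncated above 14, the variance falls by about 20%, 13% and 6% at rho 0.3, 0.5 and 0.7. The power gain is about 9, 6 and 3 percentage points. Near rho 0.9 the methods are practically equal, and any loss beyond that is negligible. The figures also treat PSS as continuous and assume complete follow-up.

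**What to change.** In section 2.7, make the primary analysis a linear model of 4-week PSS on randomised group and continuous baseline PSS, fitted whatever the observed balance. Report the adjusted mean difference with its 95% confidence interval. Do the same for GAD-7 and PHQ-9, each with its own baseline. The time × group ANOVA can remain as a supporting analysis if wanted. Any further ANCOVA covariates should be named in advance and not chosen from observed baseline differences.

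This takes one paragraph and no new data, since all three scores are already collected at baseline. The statistical price is one degree of freedom (28 to 27) and about 4% variance inflation at N = 30.

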#### 2.6.1. Primary outcome

The Perceived Stress Scale (PSS; Reis et al., 2010), is a 14-item scale used to measure the degree to which life events are experienced and appraised as stressful. Respondents are to indicate how often they have felt certain ways in the past month, with responses ranging from 0 (never) to 4 (very often).

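### Covariates for the additional ANCOVAs are chosen by chance baseline imbalance, and the only baseline test named, a Chi-square, does not suit numeric scores

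*Protocol article*

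**What the plan says.** All of the relevant analysis text is in section 2.7 of the protocol article.

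- **Baseline comparison:** after descriptive analyses of the demographics, "group differences at baseline will be analyzed using a Chi-square". No other baseline test is named.
- **Main analysis:** a time × group repeated-measures ANOVA "will be conducted to evaluate changes in stress (PSS), anxiety (GAD-7), and depression (PHQ-9) scores from baseline to 4-weeks".
- **Adjusted analysis:** "Additional analysis of covariance (ANCOVAs) will control for variables that differ between groups at baseline". The article does not define what counts as differing. Section 2.6.3 has covariates in its heading but names none.
- **Significance level:** "All ANOVAs will be tested at two-tailed alpha = 0.05". No level is given for the baseline comparisons.

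The setting is a randomised trial of 30 people. In section 2.4, "A total of 30 older adults (aged ≥ 60) will be recruited from the community, community organizations, and affiliated hospitals/clinics" and "Participants will be randomized 1:1 into the treatment group". The primary outcome, the PSS, "is a 14-item scale used to measure the degree to which life events are experienced and appraised as stressful"; items are scored 0 to 4, so the total is numeric, from 0 to 56. Section 2.6 says that "All quantitative outcomes (primary, secondary, exploratory) will be assessed at baseline and 4 weeks", so the baseline value of every outcome will be available.

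**The concern.** A covariate earns its place by its relation to the outcome, not by how unevenly it happened to fall between arms. With sound 1:1 computer randomisation, every baseline difference is a chance difference, so a rule that adjusts for whatever differs sorts variables by chance. An unrelated variable enters if it happens to be unbalanced. The baseline PSS, likely to be among the better predictors of the 4-week PSS, stays out of the ANCOVA unless its own imbalance is large enough to be noticed. The content of the adjusted model is unknown until the data are seen.

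The named test adds a second problem. A Chi-square compares counts in categories. Applied to a score with many distinct values it has almost no power, and with 15 per arm it is unreliable for uncommon categories.

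At stake is how far the adjusted results can be trusted, and whether precision that a 30-person pilot could have at almost no cost is given up.

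**Working it through.** The article gives no figure on this point, so there is nothing to reproduce. The checks below use its sample size and allocation. Three further inputs are assumptions, because the article does not state them: selection at p<0.05, independent baseline variables unless noted, and a baseline/4-week correlation of 0.5 to 0.7 with equal variances at both times.

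**1. How large must an imbalance be before the rule acts?** Suppose a t-test at 0.05 is used, with 15 per arm. The observed standardised difference must reach t(0.975, 28) × √(2/15) = 2.048 × 0.365 = 0.75 SD. Anything smaller is left unadjusted.

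**2. What does an unadjusted imbalance do?** With two time points, the time × group test is the t-test on change. Given a baseline difference of d SD and no treatment effect, the expected difference in change has size (1 − ρ)d. Just below the threshold (d = 0.75) this is 0.5 × 0.75 = 0.375 SD at ρ = 0.5, and 0.3 × 0.75 = 0.225 SD at ρ = 0.7. The arm that started higher appears to improve more.

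**3. Error rates in simulated null trials, 15 per arm.**

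| Quantity | Result |
|---|---|
| Change-score (time × group) test, all trials | 4.8 to 4.9% |
| ANCOVA with baseline fixed in advance, all trials | 4.9% |
| Selected model, baseline the only candidate | 4.3% (ρ = 0.5), 4.5% (ρ = 0.7) |
| Selected model, 10 candidates | 3.9 to 4.5% |
| Either result may be claimed, 10 candidates | 5.4 to 6.6% |
| Trials with baseline flagged: change-score test | 16 to 18% (ρ = 0.5), 12% (ρ = 0.7) |
| Trials with baseline flagged: fixed ANCOVA | 5 to 6% |

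Ranges reflect separate runs of the simulation. Baseline is flagged in about 5% of null trials.

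**4. Precision.** Relative to the variance of the 4-week score, residual variance is 2(1 − ρ) for change and 1 − ρ² for ANCOVA.

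- ρ = 0.5: 1.00 against 0.75, a reduction of 25%.
- ρ = 0.7: 0.60 against 0.51, a reduction of 15% (0.09/0.60).

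**5. How often would something be flagged by chance?** Seven scales are taken at baseline: PSS, GAD-7, PHQ-9, EQ-5D-5L, AIS, FFMQ-SF and the three-item loneliness scale. If each had a valid 5% test and they were independent, the chance of at least one spurious difference is 1 − 0.95⁷ = 30%. Simulation with a common correlation between scales gives 27% at 0.3, 23% at 0.5 and 21% at 0.6.

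**6. The Chi-square.**

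- *Numeric score* (integer values, assumed SD 7): every expected count was below 5 in all simulated trials. The test rejected 0.1% of the time with no difference and 0.2% with a true difference of 1 SD, where a t-test rejected 75%.
- *Binary variable:* the expected count per arm is half the category total, so it falls below 5 when fewer than 10 of the 30 are in the category (9/2 = 4.5). For 0/15 against 4/15, the uncorrected statistic is 30 × (0 × 11 − 15 × 4)² / (15 × 15 × 4 × 26) = 4.62, p = 0.032. With continuity correction p = 0.107, and Fisher's exact test gives 0.10. Whether the variable becomes a covariate would turn on an unstated option.

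Steps 5 and 6 are alternatives and do not add up. If the Chi-square were really applied to the seven scores, the chance of flagging any would be about 1 − 0.999⁷ = 0.7%, and the ANCOVA would almost never adjust for a scale at all.

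**The case against.** The strongest reply is that this is a supplementary analysis in a pilot. The time × group ANOVA comes first, its form is fixed in advance, and it already uses baseline PSS as its first time point. That stands: the main test is not chosen by the data, and baseline is not left out of it.

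Several stronger readings are tempting, and the article does not support them.

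- *Every baseline comparison uses a Chi-square.* The text does not say so. The clause shares a sentence with the demographics and may mean categorical demographics only, and an article may leave tests by variable type to the full plan. Even on the narrow reading, age is numeric and no other test is given.
- *Covariates are selected at p<0.05 by that Chi-square.* The article gives no threshold and does not explicitly link the two statements. The threshold is an assumption here.
- *Type I error is broken.* The calculations do not show this. The selected model is slightly conservative, and the excess appears only if either result may be claimed.
- *The article gives no indication of which model leads.* Calling the ANCOVAs additional implies that the ANOVA does. What is missing is a stated rule for when the two disagree.

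These limits reduce the size of the point. They do not rescue the rule itself, which the article states outright and did not merely leave for later.

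**Conclusion.** The point holds in a limited form. Choosing ANCOVA covariates by observed imbalance makes the adjusted model depend on chance, and the only baseline test named does not suit numeric variables or sparse categories at this sample size.

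Overall type I error is not materially affected. The cost is of two kinds. First, there is conditional bias: in the roughly 5% of null trials where baseline is flagged, the main ANOVA and the ANCOVA can disagree, and smaller imbalances, up to about 0.75 SD, get no adjustment. Second, precision is lost: at correlation 0.5 to 0.7, a fixed ANCOVA has 15 to 25% less residual variance than the change-score comparison.

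These sizes rest on assumed correlations and an assumed 0.05 threshold. That selection follows imbalance and not prognosis depends on neither. The change is worth making, but the main analysis is not invalid without it.

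**What to change.** In section 2.7:

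1. Report baseline characteristics by arm descriptively (means and SDs, or counts) and drop the baseline hypothesis tests.
2. Replace the conditional ANCOVAs with one prespecified ANCOVA per outcome. The 4-week score is the response; group and the baseline value of that outcome are the terms. Add delivery modality only if randomisation is stratified by it. Fit the model whatever imbalance is observed.
3. Do not add baseline as a covariate to the repeated-measures ANOVA, where it is already a response and would be used twice.
4. State in advance which of the two models governs the conclusion if they differ.

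The cost is a change of wording and one degree of freedom for the baseline term. No new data are needed, since section 2.6 already has every quantitative outcome measured at baseline.

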### 2.3. Waitlist control

The waitlist-control arm will complete all assessments at baseline and 4-weeks. Participants in this group will receive the meditation program once the RCT is complete.

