#### 2.6.3. Additional measures and covariates

Exploratory outcome measures will include (1) EuroQol-5 Dimension (EQ-5D-5L; Herdman et al., 2011), a standardized measure of health-related quality of life. It is a 5-component scale including mobility, self-care, usual activities, pain/discomfort, and anxiety/depression; (2) Athens Insomnia Scale (AIS; Soldatos et al., 2000) is an 8-item, self-report scale to assess sleep quality, assessing sleep induction, awakenings during the night, final awakening earlier than desired, total sleep duration, and sense of well-being during the day, sleepiness, and daytime functioning; (3) the Five Facet Mindfulness Questionnaire—Short Form (FFMQ-SF; Bohlmeijer et al., 2011) is a 24-item scale that is used to assess whether mindfulness is related to a decrease in clinical symptoms of depression, anxiety, and stress; (4) the UCLA-3 Item Loneliness Scale (Russell, 1996) measures the subjective experience of loneliness on a four-point Likert scale; (5) the Simulator Sickness Questionnaire (SSQ) Simulator Sickness Questionnaire (Kennedy et al., 1993) is a 16-item scale that is widely used to assess simulator sickness when using virtual reality. (6) the Witmer and Singer Presence Questionnaire (Witmer and Singer, 1998) is a self-report presence measure to evaluate experiential aspects of immersive technology. The latter two questionnaires will be administered at each session in the intervention group. Furthermore, participants will answer a brief questionnaire regarding their overall experience, receive summaries and references of each session for the recommended at-home practice, and will have time to ask questions at the end of each session. Additionally, qualitative data about participants’ experiences (e.g., perceptions, challenges, perceived usability), will be collected through semi-structured interviews and participant observation.

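### With PSS measured only at baseline and 4 weeks, LOCF is baseline carried forward: every dropout counts as zero change, which in general biases the treatment effect

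*Protocol article*

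**What the plan says.** Section 2.7 of the protocol article states "Missing data will be handled using the last observation carried forward (LOCF" and offers no alternative. The one analysis there called a sensitivity analysis concerns home practice, not missing data.

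Section 2.6 sets the schedule: "All quantitative outcomes (primary, secondary, exploratory) will be assessed at baseline and 4 weeks". Section 2.3 says the same of the control arm: "The waitlist-control arm will complete all assessments at baseline and 4-weeks". The only instruments used between those visits are the Simulator Sickness and Presence questionnaires (section 2.6.3): "The latter two questionnaires will be administered at each session in the intervention group". PSS is not among them.

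PSS is named as the primary outcome in section 2.6.1. Section 2.7 analyses PSS, GAD-7 and PHQ-9 by a time-by-group repeated-measures ANOVA of "scores from baseline to 4-weeks", with "All ANOVAs will be tested at two-tailed alpha = 0.05". Entry requires "Having a Perceived Stress Score (PSS) greater than 14" (Table 1).

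**The concern.** LOCF assumes that a participant's last recorded value stands in for the missing one. With a single post-baseline visit, that last value is the starting value. The rule then asserts that everyone lost to follow-up had a change of exactly zero, in both arms, whatever happened to the people who stayed.

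This is seldom neutral. If the VR programme works, dropouts in that arm pull the estimate towards zero. If stress falls in both arms for any reason, the arm that loses more people looks worse than it is. Dropout could well differ by arm: one arm attends eight headset sessions over the 4 weeks, and the other only waits. With 15 per arm, each dropout is about 7% of an arm (1/15).

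At stake are the PSS estimate, its test, and the effect size and SD that section 3 wants to pass on to larger studies.

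**Working it through.** **Plan's own figure.** There is none to reproduce. The article states a total of 30 participants, randomised 1:1, without effect size, SD, power or dropout.

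**Step 1: what LOCF does here.** PSS is recorded at baseline and 4 weeks. If the 4-week score is missing, the last observation is baseline, so the imputed change is baseline minus baseline, which is 0.

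**Step 2: effect on the estimate.** With two time points, the time-by-group test is the same as a t-test on change scores. Let pT and pC be the dropout proportions in the VR and waitlist arms, and changeT and changeC the mean changes. If missingness is unrelated to outcome:

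- expected LOCF effect = (1 - pT) × changeT - (1 - pC) × changeC
- bias = pC × changeC - pT × changeT

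The bias is zero only in special cases: no dropout, no mean change in either arm, equal dropout with no true effect, or exact cancellation.

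**Step 3: illustrative numbers.** All of these are assumptions. The true effect is -5 points, with a common fall of 3 points (changes -8 and -3) or of 1 point (changes -6 and -1).

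| Dropout VR / waitlist | Common fall 3 | Common fall 1 |
|---|---|---|
| 10% / 10% | 0.90 × (-8) + 0.90 × 3 = -4.5 | 0.90 × (-6) + 0.90 × 1 = -4.5 |
| 20% / 20% | 0.80 × (-8) + 0.80 × 3 = -4.0 | 0.80 × (-6) + 0.80 × 1 = -4.0 |
| 30% / 5% | 0.70 × (-8) + 0.95 × 3 = -2.75 | 0.70 × (-6) + 0.95 × 1 = -3.25 |
| 5% / 30% | 0.95 × (-8) + 0.70 × 3 = -5.5 | 0.95 × (-6) + 0.70 × 1 = -5.0 |

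The shrinkage under equal dropout does not depend on the common fall. The exaggeration in the last row does, and it disappears at a 1-point fall.

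**Step 4: no true effect.** The bias is (pC - pT) × common change. At 5% / 30% this is 0.25 × (-1) = -0.25 points per 1-point common fall, and -0.75 for a 3-point fall. Reversing the dropout reverses the sign. In simulation (15 per arm, SD 7, correlation 0.6, 3-point fall), type I error was about 0.07 with the imbalance in either direction and 0.048 at 20% / 20%. The sampling SD of the estimate was about 2.1 points.

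**Step 5: how much fall the entry criterion explains.** For normal scores selected above 14, regression to the mean is (1 - 0.6) × 7 × λ, where λ is the normal density divided by the upper-tail probability at (14 - source mean)/7.

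- Source mean 24: 2.8 × 0.156 = 0.4 points
- Source mean 22: 2.8 × 0.238 = 0.7 points
- Source mean 16: 2.8 × 0.625 = 1.75, or about 1.8 points

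**Step 6: power.** True effect -5, 3-point common fall, same SD and correlation, missing completely at random within arm:

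| Dropout VR / waitlist | LOCF, change score | Observed data, change score | Observed data, ANCOVA |
|---|---|---|---|
| 20% / 20% | 0.41 | 0.47 | about 0.53 |
| 30% / 5% | 0.21 | 0.47 | about 0.53 |

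The first two columns isolate LOCF. The third adds baseline adjustment, which is a separate gain.

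**Step 7: a second set of assumptions.** With changes of -6 and -2 (true effect -4) and SD of change 6, LOCF gives -3.2 at 20% / 20%, -2.4 at 30% / 10% (power 0.19, against 0.34 on observed data), -4.0 at 10% / 30% (no bias, by cancellation) and -4.4 at 0% / 20%. The pattern is the same, with different sizes.

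**The case against.** The strongest reply is that the harm is unquantified and may be small. The article gives no attrition figure. The striking results need a 25-point imbalance over only 4 weeks; at 10% per arm the estimate moves from -5 to -4.5. That stands, and it is why the figures are offered only as a range.

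A reader might infer that selecting on "Having a Perceived Stress Score (PSS) greater than 14" guarantees a sizeable fall in both arms and so makes the carried-forward score plainly wrong for every dropout. The documents do not support that. The PSS described in section 2.6.1 "is a 14-item scale used to measure the degree to which life events are experienced and appraised as stressful", with items scored 0 to 4, so the maximum is 14 × 4 = 56 and a cut-off of 14 is low. Under the assumed SD and correlation, selection alone explains about 0.4 to 1.8 points. Section 2.4 also does not say that the screening score is the baseline score. If baseline is a fresh measurement, part of that regression has already happened. A larger common fall is possible for other reasons, but none is documented.

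A reader might also credit the whole rise in power from 0.41 to 0.53 at 20% dropout to removing LOCF. Only the step to 0.47 is due to that. Nor do the imputed zeros by themselves inflate false positives: with equal dropout and no effect, type I error stays at about 0.05.

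Observed-data analysis recovers the true effect here because missingness was simulated as completely random. With outcome-related dropout it could be biased too. That is a reason for a sensitivity analysis, not for keeping LOCF.

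LOCF cannot be defended as conservative, since it can exaggerate the effect when the waitlist arm loses more people. The rule is stated outright, so it is not a detail left to an unseen analysis plan.

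**Conclusion.** The concern holds. That LOCF means baseline carried forward follows directly from sections 2.3, 2.6, 2.6.3 and 2.7 and needs no assumption. That it biases the comparison follows from the formula, outside the special cases listed.

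The size and direction are not fixed by the documents. For an assumed effect of -5 points and the dropout patterns examined, the expected LOCF estimate runs from about -2.8 to -5.5. Without a true effect, the spurious difference is about 0.25 points per 1-point common fall at a 25-point dropout imbalance. These figures rest on assumed dropout, common change and missingness unrelated to outcome; the power and type I error figures also assume SD 7 and correlation 0.6.

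This should be fixed, at moderate severity. The trial is a 30-person pilot whose aims begin with feasibility and acceptability. Against that, PSS is the named primary outcome, is tested at 0.05, and is meant to inform larger studies. It would go too far to say that the trial's result is invalid or that a false benefit is likely. GAD-7 and PHQ-9 are affected in the same way.

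**What to change.** In section 2.7, delete the LOCF sentence and state instead that:

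- observed 4-week scores are analysed with a baseline-adjusted likelihood model, either ANCOVA or a mixed model that keeps participants who have baseline only, valid under missing-at-random;
- multiple imputation with a delta shift for dropouts is the sensitivity analysis, showing how far their outcomes would have to differ to change the conclusion;
- dropout is reported by arm.

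The same wording should cover GAD-7, PHQ-9 and the exploratory outcomes measured at the same two visits.

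The cost is a few sentences and a few lines of R, with no extra participants or assessments. The downside is slightly more analysis work and reliance on missing-at-random in the main analysis, which the delta-shift analysis is there to probe.

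### Effect modification by baseline stress is planned as a two-group split of a numeric score. A continuous baseline PSS term would use the same data better if modification is roughly linear (minor)

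*Protocol article*

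**What the plan says.** Section 2.7 ends with the subgroup plan: "Additional subgroup analyses will also compare the primary outcome (PSS) between important subgroups". Two examples follow, delivery mode and "baseline stress (higher vs. lower"). No model is given for these comparisons, and no analysis in the section contains a baseline-by-arm term. The ANCOVAs in the same section only adjust for variables that turn out to differ at baseline.

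The score behind the split is described in section 2.6.1. The PSS "is a 14-item scale used to measure the degree to which life events are experienced and appraised as stressful", with "responses ranging from 0 (never) to 4 (very often") per item. Section 2.6 has all quantitative outcomes measured at baseline and at 4 weeks. The only PSS threshold in the article is the entry criterion in Table 1 (section 2.4), "Having a Perceived Stress Score (PSS) greater than 14". Everyone enrolled lies above it, so it cannot separate the two groups.

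On size, "A total of 30 older adults (aged ≥ 60) will be recruited" and "Participants will be randomized 1:1 into the treatment group" or the waitlist (section 2.4).

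**The concern.** The subgroup question is whether the benefit of VR meditation depends on how stressed a person is at entry. Cutting the score in two treats everyone within a half as alike, and treats two people on either side of the cut as different. With 15 per arm, a median split leaves 7 or 8 people in each arm-by-subgroup cell (15/2 = 7.5).

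The stake is modest. An already imprecise exploratory answer becomes less precise, although the full score is in the data set and needs no extra collection. The primary comparison and the feasibility results are not affected.

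**Working it through.** **Inputs from the article.** N = 30, allocated 1:1, so 15 per arm (section 2.4). Two-sided alpha 0.05 (section 2.7). PSS of 14 items scored 0-4, so the total runs from 0 to 14 x 4 = 56 (section 2.6.1). Entry requires PSS above 14 (Table 1).

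**Assumptions.** The article gives no SD, baseline distribution, interaction size or power for this analysis, so there is no planned figure to reproduce. Baseline distributions, slopes and residual SDs below are assumed.

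**Step 1: information kept by a split.** For a linear modifier this is the squared correlation between the score and its high/low indicator. For a normal score cut at quantile q it equals phi(z_q)^2 / [q(1 - q)].

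- Median: 0.3989^2 / 0.25 = 0.637 = 2/pi, a loss of 36%.
- 30/70 cut: 0.576 kept, a loss of 42%.
- 20/80 cut: 0.49 kept, a loss of 51%.

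At the median, the split is worth 30 x 0.637 = 19 participants analysed on the full score. Matching 30 would take 30 / 0.637 = 47.

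**Step 2: scores truncated above 14.** With integer scores split just above the median, the share kept is 0.66 (untruncated mean 26, SD 7) and 0.67 (mean 20, SD 5). Over a wider set of assumed means and SDs, with the median value itself placed on either side of the cut, it runs from 0.58 to 0.67. Shape matters: a uniform score keeps 0.75 and an exponential one 0.48.

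**Step 3: interaction power at 15 per arm.** 4-week PSS is regressed on arm, modifier and their product. Slopes are in SD of outcome per SD of baseline, and modification is linear. Results are simulated.

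| Slope | Residual SD | Continuous | Median split |
|---|---|---|---|
| 0.2 | 0.8 | about 9% | about 7% |
| 0.4 | 0.8 | 22-25% | 14% |
| 0.8 | 0.8 | about 68% | 36-37% |
| 0.4 | 1.0 | 16-17% | 11% |
| 0.8 | 1.0 | 48-50% | 27-29% |

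With no modification, both methods reject in about 5% of trials.

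**Step 4: the same comparison when linearity fails.** With residual SD 0.8 and an effect that changes in a step at the median, the two methods have equal power: 48% against 48% (mean 26, SD 7) and 49% against 49% (mean 20, SD 5).

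**The case against.** Four counter-arguments have weight.

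**The cut-point.** A reader might infer that, because no cut is stated, it will be picked after the data are seen and the false-positive rate will be inflated. The article does not support that. It condenses a full protocol, and a subgroup cut may well be fixed there or in an analysis plan that is not shown. A single pre-specified split keeps its type I error at about 5%. So the missing cut is no part of this point.

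**How much the text fixes.** The two-level comparison is one of two examples in a bracket, with no model attached, and could be shorthand. That lowers the weight of the point. Still, the article names a two-group form and nothing elsewhere in it replaces that form.

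**Linearity.** The gain is conditional. Step 4 shows that it vanishes for a step at the cut, and a plot of 15 points per arm would reveal only a gross departure. This stands as a limit on the claim.

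**Little practical gain.** At slopes of 0.2 to 0.4 neither method is likely to detect modification, and the large power gap needs the strong slope of 0.8. This stands too. It is a reason for modest claims from either analysis, but not a reason to give up a further third of the information.

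A reader might also infer that the subgroup result will decide who is recruited to a later trial. The Discussion (section 3) says only that the study will supply pilot data for larger studies. It mentions no selection by baseline stress.

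**Conclusion.** The point holds as a minor one. The article names a two-level analysis of a numeric score available for every participant. If modification is approximately linear, a split near the median keeps about two-thirds of the information on it: 64% for a normal score, 66-67% for the two assumed truncated PSS distributions. Pre-specifying the cut does not restore the loss, and for a normal score an off-centre cut loses more.

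The power figures depend on assumed SDs and slopes and should be read as a range, not as estimates for this trial. They show an advantage for the continuous score under linear modification and none under a step at the cut. This is an additional analysis in a 30-person pilot, and no primary or feasibility conclusion depends on it.

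**What to change.** In section 2.7, replace the two-group baseline-stress comparison with one model: 4-week PSS on arm, continuous baseline PSS and arm x baseline PSS. Report the interaction slope with its 95% CI, and the fitted VR-minus-waitlist difference at two or three baseline values named in advance. Label the analysis exploratory. If high and low groups are shown, use them for display only.

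The cost is one sentence of analysis wording. No new data are needed, and the model is standard in R, which the section already names. The downside is the assumption of an approximately linear interaction, which 30 participants can check only weakly, so a plot of 4-week against baseline PSS by arm should accompany the estimate. The interval will be wide, and the report should say so.
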